## Abstract

**Background:**

An anatomical reconstruction of the ankle congruity is the important prerequisite in the operative treatment of acute ankle fractures. Despite anatomic restoration patients regularly suffer from residual symptoms after these fractures. There is growing evidence, that a poor outcome is related to the concomitant traumatic intra-articular pathology. By supplementary ankle arthroscopy anatomic reduction can be confirmed and associated intra-articular injuries can be treated. Nevertheless, the vast majority of complex ankle fractures are managed by open reduction and internal fixation (ORIF) only. Up to now, the effectiveness of arthroscopically assisted fracture treatment (AORIF) has not been conclusively determined. Therefore, a prospective randomised study is needed to sufficiently evaluate the effect of AORIF compared to ORIF in complex ankle fractures.

**Methods/design:**

We perform a randomised controlled trial at Munich University Clinic enrolling patients (18–65 years) with an acute ankle fracture (AO 44 A2, A3, B2, B3, C1 - C3 according to AO classification system). Patients meeting the inclusion criteria are randomised to either intervention group (AORIF, *n* = 37) or comparison group (ORIF, *n* = 37). Exclusion criteria are fractures classified as AO type 44 A1 or B1, pilon or plafond-variant injury or open fractures. Primary outcome is the AOFAS Score (American Orthopaedic Foot and Ankle Society). Secondary outcome parameter are JSSF Score (Japanese Society of Surgery of the Foot), Olerud and Molander Score, Karlsson Score, Tegner Activity Scale, SF-12, radiographic analysis, arthroscopic findings of intra-articular lesions, functional assessments, time to return to work/sports and complications. This study protocol is accordant to the SPIRIT 2013 recommendation. Statistical analysis will be performed using SPSS 22.0 (IBM).

**Discussion:**

The subjective and functional outcome of complex ankle fractures is regularly unsatisfying. As these injuries are very common it is essential to improve the postoperative results. Potentially, arthroscopically assisted fracture treatment can significantly improve the outcome by addressing the intra-articular pathologies. Given the absolute lack of studies comparing AORIF to ORIF in complex ankle fractures, this randomised controlled trail is urgently needed to evaluate the effectiveness of additional arthroscopy.

**Trial registration:**

ClinicalTrials.gov reference: NCT02449096 (Trial registration date: April 7th, 2015).

## Background

Acute ankle fractures are one of the leading pathologies disturbing ankle congruence. These fractures are extremely common with an incidence of 0.1–0.2 % per year [1, 2]. Operative treatment performing open reduction and internal fixation (ORIF) is the standard of care for unstable or dislocated ankle fractures with the main goal of anatomical realignment of the joint and restoration of ankle stability [3, 4]. Nevertheless, even successful anatomical reduction does not automatically lead to favourable clinical outcome. According to several studies, the mid- and long-term outcome following operative treatment of acute ankle fractures is often poor [5, 6]. Residual symptoms following ankle fracture include chronic pain, stiffness, recurrent swelling and ankle instability [5, 7]. There is growing evidence that this poor outcome might mostly be related to occult articular injuries involving cartilage and soft tissues [2, 8, 9]. These intra-articular disorders have been shown to negatively affect the clinical results, but it is difficult to diagnose them by physical examination, standard radiography or CT-scans. Magnetic resonance imaging is the most reliable non-invasive diagnostic technique to identify osteochondral lesions (OCL). Nevertheless, in literature its sensitivity varies from 62 to 95 % [10–13]. In case of acute fractures to the ankle, the sensitivity is further reduced due to the traumatic oedema leading to a misjudgement of the appearance and size of OCLs [14]. In this context, many authors have emphasized the value of ankle arthroscopy [6, 7, 15]. In the last decades, it has become a safe and effective diagnostic and therapeutic procedure and has also been proposed in fracture treatment [16]. In ankle fractures, arthroscopically assisted open reduction and internal fixation (AORIF) allows a confirmation of the anatomic reduction, careful examination of the cartilage, capsular and intra-articular ligaments. If necessary, the intra-articular pathologies can immediately be addressed by removing ruptured ligaments and loose bodies, performing chondroplasty or micro fracturing if necessary [15]. There is no evidence that a supplementary ankle arthroscopy leads to a higher complication rates in ankle fracture treatment [8]. On the other hand, small or superficial chondral lesions might heal spontaneously without arthroscopic treatment. Further, the benefit of supplementary ankle arthroscopy in ankle fracture management has not yet been clearly demonstrated. There are only two randomised controlled trials evaluating the effect of additional ankle arthroscopy in isolated fractures of the distal fibula at the level of the syndesmosis (AO type 44 B1). Both documented a high incidence of intra-articular damage. In one study, patients treated arthroscopically showed significant better outcome results. Nevertheless, the vast majority of ankle fractures are managed by open procedures only [17]. Given the absolute lack of RCTs comparing AORIF to ORIF in complex ankle fractures, it is not possible to give recommendations regarding the use of additional arthroscopy up to now. However, several studies could demonstrate that the incidence of OCLs is higher the more complex the fracture is [2, 9]. Based on these findings, it is comprehensive that the effect of arthroscopy might be even more distinctive in complex ankle fractures. Therefore, we perform the first randomised controlled trial intended to report the short-, midterm- and long-term follow-up of patients who underwent operative treatment of complex ankle fractures – with and without ankle arthroscopy.

## Methods/design

### Study design

We perform a randomised controlled study to evaluate the results of the operative treatment of acute ankle fractures with and without ankle arthroscopy. This study protocol is in accordance with the SPIRIT 2013 recommendations. Patients are randomised to either ORIF (comparison) or AORIF (intervention). Patients are recruited at our hospital (level I trauma centre). PICOS criteria are depicted in detail below.**P**articipantsPatients (18–65 years) with an acute ankle fracture (AO 44-A2, A3, B2, B3, C1-3)**I**nterventionOpen reduction and internal fixation with ankle arthroscopy (AORIF)**C**omparisonOpen reduction and internal fixation without ankle arthroscopy (ORIF)**O**utcomesAOFAS (American Orthopaedic Foot and Ankle Society) Score, JSSF Score (Japanese Society of Surgery of the Foot), Olerud and Molander Score, Karlsson Score, Tegner Activity Scale, SF-12, radiographic analysis, arthroscopic findings of intra-articular lesions, functional assessments, time to return to work/sports, complications**S**tudy designRandomised controlled trial

### Patient selection

#### Eligibility criteria

Patients aged 18–65 years with an acute ankle fracture (AO 44 A2, A3, B2, B3, C1-C3) according to the judgment of the surgeons of the foot and ankle team of our level I trauma centre are enrolled in the trial. Fractures are evaluated and graded according to classification reported by AO Foundation. Patients are informed about our current investigation by detailed patient information. Only patients, who confirm in study participation and in the operative procedure, are enrolled. To avoid misclassification, all radiographs are evaluated by at least two orthopaedic surgeons. Disagreements are resolved by discussion. Only patients with a maximum interval of 2 weeks between injury and intervention are included. All patients included must be able to understand the meaning of the trial and its consequences. Written informed consent is mandatory. No additional investigation (clinical or radiographic investigation) will take place if the patient is included compared to patients who refuse inclusion. A list of inclusion and exclusion criteria can be found below (Table 1). Open fractures are excluded. Also, patients with a high risk of anaesthesiology problems (i.e., ASA risk score >3), acute infection, mental illness or low expected compliance are excluded from trial participation. If patients issue a certain treatment preference, they are excluded as well. Patients are further asked for diabetes and smoking as these are possible confounders for the outcome. Moreover, previous ankle injuries are documented in all patients.

**Table 1 Tab1:** Inclusion and Exclusion criteria

Inclusion criteria	Exclusion criteria
Age 18–65 years	Patients under 18 years or over 65 years
	Patients who have acute infections, mental illnesses, high anesthesiological risk (ASA >3)
	Patients with expected incompliance
Acute ankle fracture classified as AO type 44 A2, A3, B2, B3, C1-C3	Acute ankle fracture classified as AO type 44 A1 or B1 fracture, pilon or plafond-variant injury. Open fractures
Written informed consent (patient is able to read and understand German language properly)	Patients without written informed consent

#### Patient recruitment and screening

All patients presenting to participating surgeons with an acute ankle fracture are screened for participation in the trial. Such patients are classified as 1) excluded, if they do not meet the eligibility criteria; 2) missed, if they are presumed eligible but missed due to error or staff availability; or 3) included (eligible and randomised). Study personnel obtain written informed consent from all eligible patients.

In all patients, fractures are initially reduced, followed by plaster cast stabilization or - if this does not sufficiently reduce the fracture - by external fixator. The surgeon on charge with proven expertise in reduction and casting maneuvers performs the reduction and casting. Patients are admitted to the trauma ward afterwards in order to elevate the leg to reduce the swelling around the ankle. Operation will be performed when swelling is reduced to an acceptable level. The patient’s skin is assessed preoperatively ensuring adequate skin wrinkling.

#### Randomisation

Sequentially numbered, opaque, sealed envelopes are used for randomisation. Patients are randomised either to intervention group for arthroscopically assisted open reduction and internal fixation (AORIF) or to control group treated with open reduction and internal fixation (ORIF).

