### Statistical analysis

Primary outcome of our study is the difference of the AOFAS score between the intervention (AORIF) and comparison (ORIF) group after a follow-up of 2 years. We expect a mean difference of four points between the AORIF and ORIF group showing better results in the AORIF group. This expectation is feasible on the basis of the existing data (see [3] and [1]). The statistical calculation was performed with an expected correlation of 0.5 between the two groups. Based on a conservative estimation of the observed standard deviation of the AOFAS score in a comparable population (see [3] and [1]), we expect a standard deviation of six for the AOFAS score in our population. Based on the supposed correlation of 0.5 the standard deviation of the differences regarding our primary outcome is also expected to be not more than six. Therefore, each group has to contain 37 patients in order to find a difference of four between the two groups with a level of significance of 5 % and a power of 80 % and a standard deviation of six. In case of subgroup analysis, Shapiro-Wilk and Levene tests will be used to test normality and equality of variances. Subgroup analysis will be conducted using Student’s t-test, Pearson Chi-Square or ANOVA where appropriate. Statistics will be calculated using SPSS 22.0 (SPSS Inc. Chicago, Illinois 60606).

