## Discussion

The subjective and functional outcome of operatively treated ankle fractures is often poor [5, 6]. Winters et al. reported moderate to poor results in more than 20 % of their patients in simple, isolated fractures of the distal fibula [35]. Furthermore, Day et al. demonstrated in their long-term study, that only 52 % of the patients had good to excellent results following a bimalleolar fracture whereas 48 % of these patients only had a moderate or poor outcome after 10 years [36]. Hong et al. showed that more than 50 % of the patients with bi- or trimalleolar fractures suffered from stiffness and pain after 2 years. In the same collective 18 % did not return to sports after this period of time [37]. Recently, several determining factors for these unsatisfying results have been proposed including age, sex, severity of the fracture, size of the posterior fragment, involvement of the medial malleolus and the quality of anatomic reduction [36, 38–42]. The prerequisite for a satisfactory outcome is the anatomic reduction – at the same time it is the only risk factor that can surgically be influenced. But even anatomic restoration cannot surely prevent poor postoperative results. Based on these considerations, the unrecognized articular injuries involving cartilage and soft tissue might be the reason for these adverse clinical results [2, 8, 9]. Only since arthroscopic studies in ankle fractures exist, the incidence of chondral lesions has become evident. Chondral lesions occur in 20–89 % [3, 15]. A recent review reported chondral lesions in 495 of 782 patients (63,3 %) with more than a half of these lesions localized on the talus [43]. For instance, Hintermann et al. reported 79 % osteochondral lesion (OCL) in acute ankle fractures [5]. Leonartidis et al. found comparable rate of OCLs in their retrospective case series of 83 patients [44]. In their prospective study Stufkens et al. could demonstrate that the traumatic cartilage injury was an independent predictor for the development of posttraumatic osteoarthritis. Further they could show that chondral lesions on the lateral talus and medial malleolus were associated with worse clinical outcome [45]. Until today, there are only two randomised controlled trails evaluating the effect of additional ankle arthroscopy in ankle fractures. In contrast to our study, both studies available only included patients with isolated fractures of the distal fibula at the level of the syndesmosis (AO type 44 B1). These are the most simple fractures that are regularly treated operatively. Thodarson and co-workers found in their very small cohort that eight of nine patients had articular damage to the talar dome in the arthroscopy group [3]. They found better results in favour of AORIF although not significant after 21 months of follow-up [3]. Takao et al. enrolled 72 patients in total with 36 for each group with a follow-up of 3.5 years on average. They documented an osteochondral lesion in 74 % in the AORIF group. Furthermore, the mean AOFAS score was significantly better when patients were treated arthroscopically although the mean difference in AOFAS score was only 3.4 points [1].

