
Although arthroscopy is increasingly used in the setting of trauma for articular and periarticular fractures of the lower limb, the effectiveness of AORIF compared with ORIF has yet to be determined [46]. To date, currently available literature has not sufficiently proven that treatment of these intra-articular injuries improves outcomes over standard ORIF, as there is only few randomized controlled studies available comparing these two operative techniques. This also applies for fractures to the ankle joint - especially in case of complex fracture patterns - although the intra-articular damage is reported to be even more pronounced the more complex the fracture is [44].

Consequently, we perform the first RCT comparing AORIF to ORIF in complex ankle fractures expecting an even more distinctive effect of arthroscopy in these fracture types. By reporting the results of this first randomised controlled trail, we intend to document on the effectiveness of supplementary ankle arthroscopy in complex fractures to the ankle. By arthroscopically assisted fracture treatment we hope to improve the postoperative subjective and functional results. We believe this is of great importance as these injuries are frequent and debilitating. The main goal of our study is to identify the fracture types that will benefit from additional arthroscopy most.

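### No stratification by fracture type is described and no adjustment for it is named, so the 2-year AOFAS comparison gives up precision and protection against an unlucky draw

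*Protocol article*

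**What the plan says.** All places are in the protocol article.

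- **Randomisation:** "Sequentially numbered, opaque, sealed envelopes are used for randomisation". The section's only other content is the names of the two arms. It gives no sequence generation, blocking or stratification factor.
- **Statistical analysis:** the primary outcome is the "difference of the AOFAS score between the intervention (AORIF) and comparison (ORIF) group after a follow-up of 2 years". Student's t-test, chi-square and ANOVA are named for subgroup analysis. No covariate is named for the primary comparison.
- **Discussion, on prognosis:** "several determining factors for these unsatisfying results have been proposed including age, sex, severity of the fracture, size of the posterior fragment", followed by medial malleolus involvement and quality of reduction.
- **Discussion, last paragraph:** "The main goal of our study is to identify the fracture types that will benefit from additional arthroscopy most".
- **Eligibility criteria:** seven AO types are eligible (A2, A3, B2, B3, C1, C2, C3), and "To avoid misclassification, all radiographs are evaluated by at least two orthopaedic surgeons". Since AO type decides eligibility, it is known before an envelope is opened.

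**The concern.** The protocol treats fracture severity as a driver of outcome and fracture type as the question of most interest, and it holds a two-surgeon reading of AO class at the moment of allocation. Nothing in the text puts that reading to use, either in allocation or in the primary analysis. Table 2 schedules the AOFAS only from 6 weeks, so no baseline AOFAS could absorb a prognostic difference between arms.

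With 37 patients per arm, a realised trial may have clearly more severe fractures on one side. The estimated AOFAS difference then moves with that imbalance, and an unadjusted result is hard to defend to readers. Even in a balanced trial, leaving a prognostic factor out of the analysis wastes precision in a design with only about 80% power.

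**Working it through.** **1. The plan's own figure.** Inputs from Statistical analysis: "We expect a mean difference of four points between the AORIF and ORIF group"; "we expect a standard deviation of six for the AOFAS score in our population"; significance level 5%; power 80%. Taken as two-sided:

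n per arm = 2 × 6² × (1.960 + 0.842)² / 4² = 35.3, so 36 by the normal approximation. The two-sample t-test needs 36.3, so 37. The stated 37 per group is reproduced. Power at 37 is 80.8% (t-test) or 81.8% (normal approximation). The normal approximation is used below.

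**2. Size of chance imbalance.** Assumption: 30–50% of patients have a severe fracture; the protocol gives no share. Let K of the 74 be severe and let X of these fall in one arm of 37. Without stratification X is hypergeometric, and the gap between arms is (2X − K)/37.

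| Assumed severe share | K | SD of gap (percentage points) | P(gap ≥ 15 points) | P(gap ≥ 20 points) |
|---|---|---|---|---|
| 30% | 22 | 10.7 | 20% | 7% |
| 40% | 30 | 11.5 | 24% | 10% |
| 50% | 37 | 11.7 | 16% | 6% |

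The probabilities do not rise steadily because the gap moves in steps of 2/37. The smallest value above 15 points is 6/37 = 16.2 for K = 22 or 30, but 7/37 = 18.9 for K = 37.

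**3. What a gap does to the estimate.** Assumption: severe fractures score D points lower on AOFAS, with D from 2 to 6; the protocol gives no value. The shift is gap × D.

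- 15-point gap: 0.15 × 2 = 0.3 up to 0.15 × 6 = 0.9 points, i.e. 8–23% of the planned 4.
- 20-point gap: 0.4 to 1.2 points, i.e. 10–30% of the planned 4.

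For a 20-point gap against AORIF with 40% severe, the unadjusted test rejects when the estimate exceeds 1.96 × 6 × √(2/37) = 1.96 × 1.395 = 2.734. Conditional power is Φ((4 − shift − 2.734)/s), where s is the within-severity standard error from step 4:

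- D = 2: Φ((3.6 − 2.734)/1.376) = 74%
- D = 4: Φ((3.2 − 2.734)/1.318) = 64%
- D = 6: Φ((2.8 − 2.734)/1.216) = 52%

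Given such a gap, the conditional type I error is about 7.5% for D = 4 and 10% for D = 6. Averaged over all allocations, the mean shift is 0 and the type I error is 5.0%.

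**4. What adjustment with balanced allocation gains at 37 per arm.** If the planning SD of 6 includes the spread due to severity, the within-severity SD is √(36 − D² × 0.4 × 0.6). Then s = SD × √(2/37), and power is Φ(4/s − 1.96).

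| D | Within-severity SD | s | Power |
|---|---|---|---|
| 0 (no effect of severity) | 6.00 | 1.395 | 82% |
| 2 | 5.92 | 1.376 | 83% |
| 4 | 5.67 | 1.318 | 86% |
| 6 | 5.23 | 1.216 | 91% |

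Most of this comes from the adjustment. With adjustment but no stratification, a gap g inflates the variance by 1/(1 − g²/(4p(1 − p))). For g = 0.20 and p = 0.4 that is 1/(1 − 0.04/0.96) = 1.043, about 2% on the standard error.

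**5. By fracture type.** 74/7 = 10.6 patients per type, about 5 per arm, if the seven types are equally common (assumption). Power for 4 points with SD 6 is about 15% at 5 v 5 and 14% at 3 v 8. Balance within type barely matters at this size. With types of 10 or 11 patients, two strata reduce the chance that some type has 3 or fewer patients in one arm only from 83% to about 71%.

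**The case against.** **Silence is not a statement.** A reader might infer that all patients come from one unstratified envelope series. The article does not say so: sequential numbering describes concealment and fits several stratum-specific series equally well. A journal article may leave sequence, blocks and strata to the full protocol, and an analysis plan not shown may adjust for fracture type. This stands. It is why the point is confined to what the text describes and why the allocation part of the fix is conditional.

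**The primary test is valid.** A reader might infer that the primary comparison is biased. It is not: chance imbalance is already reflected in the standard error, and the 5% error rate holds over randomisations. This stands too. The conditional figures in step 3 describe particular unlucky draws, not the design's operating characteristics.

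**By-type results are not rescued.** A reader might infer that stratifying would secure the comparison between fracture types. Unequal arm sizes within a type cost precision but do not bias the within-type comparison. The limit is the number of patients per type, and a few strata cannot balance seven types. The by-type comparison described under Arthroscopic findings concerns lesions within the AORIF arm only, so imbalance between arms does not touch it.

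**The size rests on assumptions, and other factors compete.** The protocol gives no severe share and no AOFAS gap by severity. It also names age, sex, diabetes and smoking as possible influences, and nowhere says that AO type C is more severe than A3 or B3. This argues for leaving the grouping to the sponsor. It does not argue for leaving unused a factor that the protocol itself makes central.

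**Conclusion.** The point holds as a low-cost improvement to the primary comparison, not as an error that invalidates it. The text describes no stratification or blocking by fracture type and names no adjustment for it, although the protocol makes type and severity central and has AO class available at allocation.

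If allocation is indeed unstratified, roughly one trial in six to one in four would show a severity gap of at least 15 percentage points. Using the factor would lift power at unchanged sample size by between 1 and 9 percentage points. Both figures depend on the assumed severe share (30–50% for the gap, 40% for the power) and the assumed severity effect (2–6 AOFAS points). If severity has little effect on AOFAS, the gain is close to nil and so is the harm.

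**What to change.** 1. **Analysis.** Prespecify a grouped AO fracture type, fixed from the two-surgeon reading before the envelope is opened, as a factor in the 2-year AOFAS comparison. This needs no extra patients or data and holds whether or not allocation is stratified.
2. **Allocation.** State whether allocation is stratified. If it is not, use separate envelope series with randomly varying blocks for a small number of prespecified fracture groups, for the patients still to be randomised. The grouping is the sponsor's choice; C versus A/B is one option. Do not use seven strata with 74 patients.
3. **Claims.** Do not present either change as making the by-type comparison informative.

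The cost is a second set of envelopes, a short amendment and possibly final arm sizes that differ by one or two patients.
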